**Objective:**

We aim to (1) identify whether ECAs can persuade community-dwelling older adults to change their dietary behavior and whether ECA use can decrease loneliness, (2) test these pathways to effects, and (3) understand the use of an ECA.

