**Methods:**

The web-based eHealth app PACO is a fully automated 8-week intervention in which 2 ECAs engage older adults in dialogue to motivate them to change their dietary behavior and decrease their loneliness. PACO was developed via a human-centered and stakeholder-inclusive design approach and incorporates Self-determination Theory and various behavior change techniques. For this study, an unblinded randomized controlled trial will be performed. There will be 2 cohorts, with 30 participants per cohort. Participants in the first cohort will immediately receive the PACO app for 8 weeks, while participants in the second cohort receive the PACO app after a waiting-list condition of 4 weeks. Participants will be recruited via social media, an online panel, flyers, and advertorials. To be eligible, participants must be at least 65 years of age, must not be in paid employment, and must live alone independently at home. Primary outcomes will be self-assessed via online questionnaires at intake, control, after 4 weeks, and after 8 weeks, and will include eating behavior and loneliness. In addition, the primary outcome—use—will be measured via data logs. Secondary outcomes will be measured at the same junctures, via either validated, self-assessed, online questionnaires or an optional interview.

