### Research Questions

Our research questions focus on both use and health outcomes. The research questions related to use are as follows: (1) What factors affect the use of the ECA? (2) Does use affect the users’ relationship with the ECA? (3) What is the use of PACO over time? (4) How do users experience PACO use? We will test the CEU to answer research question (RQ) 1 and 2. Via data log analyses (RQ3) and interviews (RQ4) we aim to explain the findings related to the CEU. This way, we will triangulate results.

The research questions related to health effects are as follows: (1) To what extent does PACO reduce loneliness and improves eating behavior and, ultimately, QoL? (2) To what extent does PACO increase autonomy, competence, and relatedness? (3) How does PACO use affect the loneliness and eating behavior of older adults? We will test the CHE to answer RQ1. For RQ2 and RQ3, we will compare the effect of using PACO at different time points, including control.

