### Data Collection

The main study parameters include use, eating behavior, and loneliness. Use will be assessed via data logs, which will be collected by the PACO app. More specifically, data logs contain the user ID, timestamp, dialogue, and ECA (either Ellen or Herman). In addition, data logs contain the number of goals achieved, the diary input, and the chat history. Eating behavior will be self-assessed by 3 open questions, based on a 24-hour recall format. The questions include the following: (1) Did you eat fruit yesterday? If so, what kinds of fruit, what time, and how many grams per piece? (2) Did you eat vegetables yesterday? If so, what kinds of vegetables, what time, and how many grams per piece? (3) Did you drink yesterday? If so, what kinds of drink, what time, and how many glasses, cups, or milliliters? Loneliness will be self-assessed via a questionnaire (Table 3).

**Table 3 table3:** Details of the questionnaires.

Factor	Questionnaire	Items, n	Scale	Modifications
Loneliness	De Jong Gierveld Loneliness Scale [47]	6	1-5	None
Autonomy, competence, and relatedness	Basic Psychological Need Satisfaction and Frustration Scales [48-50]	24	1-5	None
QoL^a^	Brief Older People’s Quality of Life [51]	13	1-5	Translated to Dutch
Relationship with ECA^b^	Rapport Scale [52-54]	10	1-5	Translated to Dutch; ‘virtual coach’ instead of ‘coordinator’
Usability	System Usability Scale [55]	10	1-5	Translated to Dutch
Enjoyment	Affect Scale [56]	4	1-5	Translated to Dutch
Aesthetics	Classic Aesthetics [21]	5	1-7	Translated to Dutch
Privacy concerns	Concern for Privacy Scale [24]	4	1-7	Translated to Dutch
Control	Active Control [57]	4	1-7	Translated to Dutch; ‘PACO’ instead of ‘website’
Perceived usefulness	Perceived Usefulness Scale [28,58]	3	1-5	Translated to Dutch; ‘PACO’ instead of ‘the robot’

^a^QoL: quality of life.

^b^ECA: embodied conversational agent.

The secondary study parameters include self-determination (autonomy, competence, relatedness), QoL, relationship with ECA, usability, enjoyment, aesthetics, privacy concerns, control, and perceived usefulness. All these parameters will be measured via validated, self-assessed, online questionnaires.

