### Data Analysis

Descriptive statistics will be used for participant demographics, data logs, and willingness-to-pay data. Data logs will be used to determine the frequency of login, time spent on each module, time spent in total, time of use, and time of dropout. If a participant has not interacted with PACO for 14 consecutive days, they will be treated as a dropout and omitted from further analysis. The within-subject *t* test will be used to compare effects between control, T0, T1, and T2. PLS-SEM will be used in 2 phases per model to test the conceptual models. In phase 1, the measurement model will be validated by testing the constructs separately to determine internal validity [using structural equation modeling (SEM)-oriented criteria and a traditional Cronbach alpha]. In addition, it will be determined whether there is multicollinearity. If there is an acceptable measurement model, phase 2 will be carried out. The causal model will be tested and, if necessary, optimized. A conservative approach will be adopted whereby the theoretical model will be adjusted only if this results in a large improvement in the model. The quality of the causal model will be determined on the basis of PLS-SEM specific goodness-of-fit indices. All analyses will be performed in SPSS (version 24; IBM Corp) and SmartPLS (version 3; SmartPLS GmbH).

Audio recordings of the interviews will be transcribed until data saturation is reached. The transcripts of, and answers to, the open user-experience questions will be uploaded in ATLAS.ti qualitative data analysis software (version 8.4; ATLAS.ti Scientific Software Development GmbH). Analysis will be guided by a thematic analysis approach [59], combining a deductive and an inductive approach. The protocol for the focus group will be used to generate deductive codes. An initial list of inductive codes will be generated by LK and supplemented independently by another researcher. Differences will be discussed, leading to a final and agreed upon codebook. Each transcript will be coded by LK and another project member. Differences will be discussed again, leading to a final coded transcript.

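### The time-point t tests on the two primary health outcomes have no fixed deciding contrast, and the three eating questions have no single endpoint, so the chance of a false-positive primary result exceeds 5% on every reading checked

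*Protocol article*

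**What the plan says.** - **Primary outcomes.** Data Collection states: "The main study parameters include use, eating behavior, and loneliness". The Abstract also lists eating behavior and loneliness as primary. Use is taken from data logs and analyzed descriptively, so it adds no test.
- **Eating behavior.** "Eating behavior will be self-assessed by 3 open questions, based on a 24-hour recall format". The questions cover fruit, vegetables and drinks. The article gives no combined score and no lead component.
- **Test.** Data Analysis gives one sentence: "The within-subject *t* test will be used to compare effects between control, T0, T1, and T2". It names no outcome and no pair.
- **Which questions the comparisons serve.** Research Questions says: "For RQ2 and RQ3, we will compare the effect of using PACO at different time points, including control". Among the health questions, RQ3 concerns loneliness and eating behavior; RQ2 concerns autonomy, competence and relatedness. RQ1 (loneliness, eating behavior and, ultimately, QoL) goes elsewhere: "We will test the CHE to answer RQ1".
- **Objective 1.** The Abstract's aim is to "identify whether ECAs can persuade community-dwelling older adults to change their dietary behavior and whether ECA use can decrease loneliness".
- **Design.** 60 participants, 30 per cohort. Only cohort 2 completes the control questionnaire, before its 4-week wait.

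**The concern.** The article commits to an analysis but leaves open which part of it answers the question. The candidate contrasts can disagree: loneliness might fall from T0 to T1 and return by T2, or fruit intake might rise while vegetable intake does not. Nothing in the text says in advance which result would count. A reader of the trial report could not tell whether a reported significant pair was the planned one or the favorable one. The error rate of a statement about a primary outcome would then be set by how many pairs and food results were examined, not by the level of a single test.

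**Working it through.** The article states no error rate, so there is no figure of its own to reproduce. The check asks how often an inert app yields at least one p < 0.05 among the primary health tests.

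**Inputs from the article**
- Four occasions (control, T0, T1, T2): 4 x 3 / 2 = 6 pairs per outcome.
- Tested primary outcomes: 2 if eating behavior is scored as one variable, or 1 + 3 = 4 if loneliness, fruit, vegetables and drinks are tested separately.
- Largest families: 2 x 6 = 12 tests, or 4 x 6 = 24 tests.
- Numbers: 30 for pairs that use the control questionnaire, 60 for pairs among T0, T1 and T2.

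**Assumptions (not in the article)**
- Two-sided 0.05 per test and no true change at any time.
- Correlation of 0.5 across time. Values of 0.7 and 0.8, and an autoregressive pattern at 0.7, changed the rates little.
- Correlation between outcomes from 0 to 0.8.

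**Upper reference.** If all tests were independent, the rate would be 1 - 0.95^m: 1 - 0.95^12 = 46% and 1 - 0.95^24 = 71%. Pairs of time points share data, so the true rates are lower and were simulated (multivariate normal data, paired t tests, several thousand null trials per setting).

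**Chance of at least one p < 0.05**

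| Pairs tested per outcome | Two outcomes | Four results |
|---|---|---|
| All six | 31-39% | 43-64% |
| T0/T1/T2 pairs only (three) | 18-24% | 26-41% |
| One contrast | 8-10% | 12-19% |

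The low end of each range is at between-outcome correlation 0.8 and the high end at 0. The one-contrast row agrees with the formula at independence: 1 - 0.95^2 = 9.8% and 1 - 0.95^4 = 18.5%. One outcome with all six pairs gives about 21-23%. With 20 or 24 per cohort instead of 30, the six-pair rates hardly change.

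**Benefit claims only.** Control to T0 lies before cohort 2 receives the app, and a two-sided result can point to harm. Leaving out control to T0 and counting only the favorable direction, at outcome correlation 0.5, gives about 18% (two outcomes) or 29% (four results). The matching benchmark for a single test is 2.5%.

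**With the fix.** Two outcomes at 0.025 each give 1 - 0.975^2 = 4.9% if independent. Holm keeps the family at or below 5% whatever the correlation.

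**Power cost (noncentral t, 80% power)**
- Two-sample, 30 v 30: detectable effect 0.74 SD at 0.05 and 0.81 SD at 0.025.
- Paired, 60 people: 0.37 and 0.41 SD of the change.

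**The case against.** The strongest reply is that this is a condensed article for a study it calls explorative, sized by a rule for PLS-SEM, and that alpha, multiplicity and scoring often sit in an analysis plan that is not shown. Part of that stands: a missing adjustment method alone would be a weak point. What remains is that the article does state the time-point rule, and that rule leaves the deciding contrast and the eating endpoint open. The explorative label appears once, as a reason for the sample size. The t tests are not labelled exploratory, and objective 1 asks whether the app works.

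Four stronger readings are tempting, and the document does not support them.
- **One headline rate.** A reader might infer that the plan has a single known false-positive rate. The rate depends on an assumed alpha, the pairs tested, the number of eating results and the correlations.
- **Every health outcome.** A reader might infer that all health scales are t-tested across all pairs. The sentence in Data Analysis names no outcome, and QoL appears only under RQ1, which is answered by the conceptual model explaining health effects (CHE). That model also bears on loneliness and eating behavior, so the t tests are not shown to be the only basis for objective 1.
- **Any significant pair counts as an effect.** The article does not say this. It only fails to exclude it.
- **Between-cohort tests would leave the problem as large.** Both cohorts have the app after the 4-week wait, so there is only one between-cohort contrast against people without it. With one contrast, about 8-10% (two outcomes) or 12-19% (four results) remains.

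**Conclusion.** The point holds for the two primary health outcomes. The stated rule allows several time-point contrasts and up to three eating results with none named as deciding. At an assumed two-sided 0.05, the chance of at least one nominally significant primary result under no true change runs from about 8% (one contrast, two outcomes) to about 64% (six pairs, four uncorrelated results). Every reading checked exceeds 5%, so the conclusion does not depend on the six-pair count. The size does, and any figure should be quoted with its conditions. The chance of a false claim of benefit is roughly half the six-pair rate. These rates assume no change over time; drift unrelated to the app would raise them. The plan should be changed, but the gap does not in itself invalidate the trial.

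**What to change.** In Data Analysis:
- Name one deciding contrast for each primary health outcome: the randomized 4-week change, cohort 1 from T0 to T1 against cohort 2 from control to T0. It uses data already planned.
- Name one eating-behavior endpoint, for example grams of fruit plus vegetables, with drinks secondary.
- Test loneliness and that endpoint by Holm at a two-sided family-wise 0.05.
- Label all other time-point pairs, the separate food results and the secondary scales as exploratory, reported as estimates with 95% confidence intervals.
- State how these tests and the CHE model share the answer to objective 1.

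The cost is a few sentences and no new data. Under Holm the smaller p-value must be below 0.025, so the effect detectable with 80% power rises from about 0.74 to at most 0.81 SD in 30 v 30. If a paired test in 60 people is kept instead, it rises from 0.37 to 0.41 SD of the change.

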### Procedure

Interested people can visit a website to view more information, or they can contact the researchers. People can choose to receive the information letter and consent form by post (Multimedia Appendix 1) or view and complete the form online. After providing informed consent, participants will be invited to complete the intake questionnaire. In this questionnaire, they will be asked to report their demographics (gender, age, educational level, health conditions, risk of malnutrition [35], and eHealth literacy [36]), whether they own a device to use for the study, and their motivation to participate. A copy of the signed informed consent will be sent to all participants by mail. The researchers will mail people who do not return the informed consent by post to check whether something has gone wrong or they do not wish to participate (no explanation will be required).

After completing both the informed consent and the intake questionnaire, participants will be assigned a random 4-digit research number. To allocate participants to a cohort, they will be randomly assigned a digit, either 1 or 2, in a list generated by Excel (version 16.0.13426.20274; Microsoft). Participants will receive an email from author LK containing their research number, information on their allocated cohort, and a copy of the information letter and the signed informed consent.

Participants in cohort 2 will first be asked to complete the additional control questionnaire (Table 1) and will start the intervention period after 4 weeks. At the start of the intervention period, participants will receive an email with instructions for the onboarding process. The email will contain a video message from the researchers introducing themselves and the project, as well as a link to the freely available PACO website. Once participants have created an account, they will be asked to complete the T0 questionnaire, assessing the health parameters and relationship with the ECA. Participants will be phoned within 2 working days and asked whether they have any questions. If a participant does not wish to be called, this can be indicated by email. If a participant needs help, the researchers will offer to visit the participant. A logbook will be kept of all such contacts. If participants do not have a tablet or a computer, they will be given a tablet for the duration of the study.

**Table 1 table1:** Metadata and factors measured via questionnaires, per study phase.

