**Figure 4 figure4:**
[figure not shown]
PACO app home screen.

**Table 2 table2:** The modules of the PACO app.

Week	Module	Behavior change technique	SDT^a^ component, target behavior	Rationale
1	Food diary	Self-monitoring	Autonomy, eating behavior	Users record what they have eaten, with whom, and how they appreciated the meal. There is an option to set reminders. When users know what they eat and drink, we aim to give them the feeling that they are able to change their behavior [37], leading to an actual change in eating behavior.
2-8	Goals	Action planning	Competence, eating behavior and loneliness	Users can choose from a list of social and eating goals. Via dialogue, Ellen explains the goal and provides tips. Users create a personal action plan and track their progress, with the option to set reminders. When users carry out their plans, we aim to improve their feelings of competence [31], leading to changes in eating behavior and feelings of loneliness.
1-8	Recipes	Tailoring and self-efficacy	Autonomy, eating behavior	Via dialogue, Herman helps users select a healthy and easy-to-prepare recipe (>280), based on users’ dietary wishes and preferences. By assisting users in cooking their own meals in line with their preferences, we hope to increase feelings of autonomy via self-efficacy [38], leading to a change in eating behavior.
1-8	Stories	Social learning	Relatedness, loneliness	Users can listen to stories from other older adults about physical or virtual social activities they perform. Ellen can provide more information on the activity. When users learn from each other, we hope that they will feel more related to others and have fewer feelings of loneliness [39,40].
1-8	Chat	Social facilitation (peer support)	Relatedness, loneliness	Via WhatsApp groups, users can interact with one another. Ellen is also included and asks questions. When users interact with one another, we hope that they will experience increased feelings of relatedness and decreased feelings of loneliness [41,42].

^a^SDT: Self-determination Theory.

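### Loneliness and relatedness changes may correlate within WhatsApp chat groups, and the named within-subject t test makes no allowance for this at T1 or T2

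*Protocol article*

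**What the plan says.** Allocation is individual (Procedure): "To allocate participants to a cohort, they will be randomly assigned a digit, either 1 or 2, in a list generated by Excel". Delivery is partly in groups. Table 2 describes the Chat module thus: "Via WhatsApp groups, users can interact with one another". One of the two agents also takes part in the groups and puts questions to them. The same row gives the mechanism: "When users interact with one another, we hope that they will experience increased feelings of relatedness and decreased feelings of loneliness".

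Data Collection gives loneliness primary status: "The main study parameters include use, eating behavior, and loneliness". Relatedness is listed there among the secondary parameters. Data Collection also says that the chat history is logged.

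For the comparison of time points, Data Analysis commits to this: "The within-subject *t* test will be used to compare effects between control, T0, T1, and T2". It mentions no chat-group term for that test. PLS-SEM is planned separately for the conceptual models, also without a group structure. Under Limitations, the article recognises that invited relatives may contaminate one another and promises monitoring; chat groups are not mentioned there.

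**The concern.** A within-subject t test is a one-sample t test on each person's change. Its standard error is the standard deviation of the changes divided by the square root of the number of people, which is right only if one person's change says nothing about another's. The Chat module is meant to work through members' influence on each other, and members of a group also share the agent's prompts. A lively group may move together, and so may a silent one.

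If so, 60 changes carry less information than 60 independent ones. The loneliness result after four and eight weeks of use, one of the trial's main results, could look more certain than it is. Without recorded group membership, nobody could show afterwards that the correlation was negligible.

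**Working it through.** **Figure to reproduce.** None exists for this test: the article gives no alpha, effect size, standard deviation or power for the t test. The total of 60 comes from the 10-times rule for PLS-SEM (Participants).

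**Inputs from the article.** N = 60, 30 per cohort (Participants). Within-subject t test (Data Analysis). Interacting chat groups aimed at loneliness and relatedness (Table 2). T0 marks the start of the intervention (Study Design).

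**Assumptions, since the article is silent.** Two-sided nominal 5%; group size m of 5 or 10; ICC of the changes 0, 0.01, 0.05 or 0.10; equal groups; everyone uses Chat.

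**Formulas.**
- Design effect: DE = 1 + (m − 1) × ICC
- Effective sample size: N / DE
- True error of the unadjusted test: about 2 × [1 − Φ(1.96 / √DE)]

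**Worked case, m = 10 and ICC = 0.05.** DE = 1 + 9 × 0.05 = 1.45. Effective N = 60 / 1.45 = 41.4. 1.96 / √1.45 = 1.63, so the true error is about 10.4%.

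**Check by simulation.** 20,000 null data sets per setting with N = 60, compared with a t test on group means:

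| m | ICC | DE | Effective N | Error, formula | Error, simulated | Group-mean t test |
|---|---|---|---|---|---|---|
| 5 | 0.01 | 1.04 | 57.7 | 5.5% | 5.3% | 4.9% |
| 5 | 0.05 | 1.20 | 50.0 | 7.4% | 7.5% | 5.2% |
| 5 | 0.10 | 1.40 | 42.9 | 9.8% | 9.9% | 5.1% |
| 10 | 0.01 | 1.09 | 55.0 | 6.0% | 6.1% | 4.9% |
| 10 | 0.05 | 1.45 | 41.4 | 10.4% | 10.4% | 5.2% |
| 10 | 0.10 | 1.90 | 31.6 | 15.5% | 15.4% | 4.7% |

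At ICC 0 the unadjusted test kept its level (4.8% to 5.1%). With one cohort (N = 30) and groups of 10, the errors were nearly the same: 10.2% at ICC 0.05 and 15.4% at ICC 0.10.

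**Partial uptake.** Suppose half of the 60 use Chat, in 6 groups of 5 active members, at ICC 0.05. Then DE = (60 + 6 × 5 × 4 × 0.05) / 60 = 66 / 60 = 1.10. 1.96 / √1.10 = 1.87, so the true error is about 6.2%. Had these been counted as groups of 10 with everyone active, the answer would have been 10.4%.

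**Which comparisons are affected.** Cohort 2 completes the control questionnaire before its four-week wait and T0 at the start of use, so the control-to-T0 change involves no chat contact. Under PACO App, the modules other than the diary open after seven completed diary days, or after 14 days at the latest; Table 2 lists Chat for weeks 1 to 8. On either account Chat is available before T1 and T2, so the issue attaches to changes that end at T1 or T2.

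**The case against.** The strongest reply is that the harm is conditional. It needs a positive ICC, groups of some size and real use of Chat, and the article gives none of these. Chat is optional and is one of five modules. Goals and Stories also target loneliness, and neither is described as working through chat groups. If Chat opens only after one or two weeks, T1 follows just two to three weeks of contact. If Chat moves nobody, it creates no correlation; inflation arises when groups move in different directions around a zero average. All of this stands. It limits the size and could make it negligible, but it does not change the direction of the error.

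It is also said that the study is described as explorative and that a group term could sit in an analysis plan not shown here. That is possible. But the article names the test, and that test as named assumes independence. The point is therefore about a stated choice rather than a missing detail.

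Three stronger readings are tempting and are not supported:
- A reader might infer error rates of 20% or more. Those require one group of 30 per cohort with everyone in it (20.6% at ICC 0.05, 32.5% at ICC 0.10), and the article nowhere says that groups are formed so.
- A reader might infer that the sample size wrongly omitted a design effect. The 60 was set by a PLS-SEM rule, so there is no t-test power calculation from which one could have been left out.
- A reader might infer that every loneliness and relatedness comparison is affected. Cohort 2's control-to-T0 comparison is not.

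**Conclusion.** The concern holds in conditional form. The Chat module gives a specific reason, stated by the article itself, to expect changes in loneliness and relatedness to correlate within chat groups, and the test named for those changes ignores it. If the correlation is positive, p-values are too small and intervals too narrow for comparisons involving T1 or T2. With full uptake and N = 60, the true error at a nominal 5% runs from about 5.3% (groups of 5, ICC 0.01) through about 10% (groups of 10, ICC 0.05) to about 15% (groups of 10, ICC 0.10). Low uptake brings it down. Group size, ICC and uptake are all assumptions, so it cannot be said that the reported p-values will be too small, only that they may be and that the plan as written could not tell.

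**What to change.** 1. Keep a chat-group identifier for each participant with the chat history already logged, and report the number, size and active membership of the groups.
2. In Data Analysis, replace the t test for loneliness and relatedness changes ending at T1 or T2 with a mixed model in SPSS that has a random intercept for chat group and Satterthwaite degrees of freedom. Where several time points enter one model, add a random intercept for participant. Treat each non-user of Chat as a singleton cluster. Cohort 2's control-to-T0 comparison needs no chat-group term.
3. If too few groups form to estimate the group effect (set the threshold in advance; about four is a workable choice), report as a sensitivity analysis intervals widened by √[1 + (m − 1) × ICC] over a stated ICC range such as 0.01, 0.05 and 0.10. Do not rest the loneliness claim on the unadjusted p-value alone. With a single group in a cohort, the group effect cannot be separated from the effect of PACO in that cohort.

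Delivery of the intervention need not change. The cost is one data field and a revised sentence in the analysis text, with no extra participants or visits. The downside is somewhat wider intervals: by a factor of √1.04 = 1.02 for groups of 5 at ICC 0.01, √1.45 = 1.20 for groups of 10 at ICC 0.05, and √1.90 = 1.38 for groups of 10 at ICC 0.10, with a little more where few groups leave few degrees of freedom.

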## Methods

### Study Design

An unblinded randomized controlled trial will be carried out. At the time of study protocol submission, all preparations have been made to start recruitment. There will be 2 cohorts (Figure 3). Participants in the first cohort will receive the 8-week PACO app immediately. Participants in the second cohort will receive the PACO app after a 4-week waiting-list condition and serve as a control group. A combination of various data collection methods will be used for this study, including questionnaires (control, at intake, T0, T1, and T2), data log collection during the intervention period, and an optional interview afterward. The T0 questionnaire will mark the start of the intervention, T1 will be completed after 4 weeks of use, and T2 after 8 weeks of use (Figure 3).

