### Participants

We aim to include a total of 60 participants: 30 in cohort 1 and 30 in cohort 2. The number of participants is based on the 10-times rule, a widely used minimum-sample-size estimation method for partial least squares structural equation modeling (PLS-SEM) [32]. This method was discussed with a statistician. In addition, we considered the current practices in the field [12], the explorative nature of this study, and the staff available to provide support.

Participants will be considered eligible if they are aged 65 years or older, are not in paid employment, and live alone independently at home. These inclusion criteria fit a potential target audience of almost 1 million people [33]. In addition to these criteria, participants need to speak Dutch to use the app, should be able to use a tablet or computer by themselves, and should have a wireless internet connection at home, which is required for the app. The latter 2 criteria seem feasible, as 94.5% of all older Dutch adults aged 65-75 years have internet access at home, with 77% using the internet daily [34]. Apart from willingness to provide informed consent, there are no exclusion criteria.

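### The only test named for comparing outcomes is within-subject, so the randomised 4-week contrast between immediate PACO and the waiting list is set up but not tested

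*Protocol article*

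**What the plan says.** Study Design in the protocol article states: "An unblinded randomized controlled trial will be carried out". It gives the second cohort its role: "Participants in the second cohort will receive the PACO app after a 4-week waiting-list condition and serve as a control group". The Participants section sets the size: "We aim to include a total of 60 participants: 30 in cohort 1 and 30 in cohort 2".

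The measurement schedule is as follows.

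- Study Design: "The T0 questionnaire will mark the start of the intervention, T1 will be completed after 4 weeks of use, and T2 after 8 weeks of" […].
- Procedure: "Participants in cohort 2 will first be asked to complete the additional control questionnaire (Table 1) and will start the intervention period after 4 weeks".
- Table 1: eating behavior and loneliness are collected at all four occasions (control, T0, T1, T2).

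Three statements bear on how health effects will be analysed.

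- Data Analysis: a within-subject *t* "test will be used to compare effects between control, T0, T1, and T2".
- Research Questions, for health questions 2 and 3: "we will compare the effect of using PACO at different time points, including control".
- Research Questions, for health question 1 (loneliness, eating behavior and quality of life): "We will test the CHE to answer RQ1". The CHE is the conceptual model of health effects, tested by PLS-SEM. The text gives it no term for cohort.

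Data Analysis also drops from further analysis anyone who has not interacted with PACO for 14 consecutive days.

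**The concern.** Randomisation gives one comparison protected from whatever else changes over a month: four weeks of PACO against four weeks of waiting. The named test does not use it. A paired test asks whether people changed, not whether they changed more than they would have without the app.

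The distinction matters here because the outcomes are self-reported in an unblinded trial of volunteers, and eating behavior rests on a recall of the previous day. Season and repeated questionnaires can shift such measures with no help from the app, and a paired T0-T1 test cannot separate that shift from a PACO effect. The first objective is whether ECAs can change diet and reduce loneliness. Under the stated analysis, the answer would rest on before-after change in a trial reported as randomised and controlled.

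**Working it through.** **1. What each comparison uses, by calendar time from allocation**

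| | Start | Week 4 | Week 8 | Week 12 |
|---|---|---|---|---|
| Cohort 1 | T0 | T1 (4 weeks of PACO) | T2 (8 weeks of PACO) | – |
| Cohort 2 | Control | T0 (end of wait) | T1 (4 weeks of PACO) | T2 (8 weeks of PACO) |

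- A within-subject comparison with control can only be made in cohort 2 (planned n = 30).
- Control to T0 in cohort 2 shows change in untreated people. The plan does not set it against T0-T1.
- T0-T1 and T0-T2 have no comparator in either cohort.
- The randomised contrast is cohort 1 at T1 against cohort 2 at T0, both at week 4. It is not named.
- At week 8, cohort 2 has already had 4 weeks of PACO, so 8 weeks of use has no concurrent untreated control.

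**2. False-positive rate of the paired T0-T1 test when PACO does nothing**

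The article gives n = 30 per cohort and 60 in total. It gives no drift, correlation or significance level. Assumed: two-sided 5%, equal SDs at both occasions, correlation r = 0.5 to 0.7, a common drift δ in SD units per 4 weeks, and no dropout. The article does not say whether cohorts are pooled, so both n = 30 and n = 60 are shown.

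The SD of a change score is √(2(1−r)), so the noncentrality is δ√n / √(2(1−r)). For δ = 0.2:

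- n = 30, r = 0.5: 0.2 × 5.477 / 1.000 = 1.10; noncentral *t* on 29 df gives 18.5%.
- n = 60, r = 0.7: 0.2 × 7.746 / 0.775 = 2.00; noncentral *t* on 59 df gives 50.3%.

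| Drift δ | n = 30, r = 0.5 / 0.7 | n = 60, r = 0.5 / 0.7 |
|---|---|---|
| 0.05 SD | 5.8% / 6.4% | 6.7% / 7.8% |
| 0.1 SD | 8.3% / 10.5% | 11.9% / 16.6% |
| 0.2 SD | 18.5% / 27.7% | 33.2% / 50.3% |

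**3. The same check for the randomised contrast**

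Drift common to both cohorts cancels in the difference between them. In a simulation of 20,000 trials per setting (30 against 30, *t* test on 4-week change, drift 0 to 0.4 SD, r = 0.5 and 0.7), rejection was 4.9% to 5.3%. In an ANCOVA, common drift goes into the intercept and leaves the cohort coefficient unchanged.

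**4. What the randomised contrast can detect**

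With 30 per cohort, two-sided 5% and 80% power, the unadjusted *t*-based detectable difference is 0.736 SD. Baseline adjustment multiplies it by √(1−r²):

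- r = 0.5: 0.736 × 0.866 = 0.64 SD
- r = 0.7: 0.736 × 0.714 = 0.53 SD

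For comparison, a pooled paired test (n = 60, normal approximation) appears to detect 2.802 × √(2(1−r)) / √60, which is 0.36 SD at r = 0.5 and 0.28 SD at r = 0.7. That advantage comes from assuming zero drift.

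**The case against.** **The wait-period change measures drift.** In part it does. The paired control-T0 comparison in cohort 2 estimates change in untreated people, so a reader who infers that the plan is blind to every time trend goes too far. But the plan does not set that change against T0-T1. If it did, the comparison would be sequential within one cohort, not the randomised one.

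**Health question 1 is assigned to the CHE model, not the *t* test.** This is correct. However, the text describes no cohort contrast in that model, and its figure is not available here. A model of paths among constructs does not become a randomised comparison unless allocation enters it.

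**The study is explorative, sized for PLS-SEM, and an analysis plan may exist.** Both sizing statements hold, and details may sit elsewhere. But the article states a particular test and the Research Questions section agrees with it. That is a stated choice, not silence.

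**Extra attention would still count as effect.** This stands. Calls at onboarding and after 7 inactive days accompany PACO use, and no matching contact is described for the wait. A reader might infer that the choice of test causes this problem. It does not: the between-cohort comparison carries it too.

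**Multiplicity.** A reader might infer that every pair of the four occasions is tested on each outcome. The article does not say so, and handling of multiple tests is commonly left to an analysis plan. No error rate across tests is claimed here.

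**The two baselines are not identical in setting.** T0 follows the onboarding email, video and account creation, while the control questionnaire does not. So cohort 2's T0 is not a pure end-of-wait measure. This is a caveat to report, and it does not favour the paired test.

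**Conclusion.** The point holds in this form: the stated outcome comparison is within-subject, the control questionnaire exists in one cohort only, and the randomised 4-week contrast is not tested. This follows from the text without any assumption.

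The size of the resulting error does depend on assumptions. For r = 0.5 to 0.7 and n = 30 to 60, the paired T0-T1 test is falsely significant in about 6-8% of trials at a drift of 0.05 SD, 8-17% at 0.1 SD and 19-50% at 0.2 SD, against about 5% for the between-cohort test. The article gives neither drift nor correlation, so no single figure should be quoted, and with very small drift the inflation is slight.

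Two stronger conclusions are not supported. Changing the test would not remove the effect of extra study contact. Nor would it supply a control for the 8-week results. Both are limits of the design.

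**What to change.** In Data Analysis:

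1. Make the primary effect analysis for loneliness and eating behavior an ANCOVA comparing cohort 1 at T1 with cohort 2 at T0 (end of the wait). The baseline covariate is T0 in cohort 1 and the control questionnaire in cohort 2. Eating behavior is collected as three open questions, so state the score or scores to which this applies.
2. Analyse participants as randomised, and do not apply the 14-day inactivity exclusion to this analysis. That rule is a separate provision and needs its own edit.
3. Keep the within-subject changes as secondary and labelled uncontrolled, including every 8-week result.
4. Report the detectable difference, about 0.53-0.64 SD at 80% power for r = 0.7 to 0.5 with 30 per cohort, beside the 10-times rule.
5. State as design limits the extra study contact during PACO use and the different circumstances of the two baseline questionnaires.

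No new data are needed, because Table 1 already schedules both outcomes at control, T0 and T1. The cost is two text changes (the test and the exclusion rule) and a less favourable detectable difference than the paired test appears to offer. The gain is protection from common time trend and repeated-measurement effects over the first 4 weeks.
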